### MRI data analysis

MRI data will be processed using multiple software packages including FMRIB Software Library (FSL; http://fsl.fmrib.ox.ac.uk/fsl), Analysis of Functional NeuroImages (AFNI; https://afni.nimh.nih.gov/afni), FreeSurfer (http://freesurfer.net), and Statistical Parametric Mapping (SPM; http://www.fil.ion.ucl.ac.uk/spm).

#### Voxel-based morphometry (VBM) analysis

The structural T1-weighted MRI data will be used in a VBM analysis using SPM. Tissue classification, registration, and bias correction will be processed in a generative model. Nonlinear deformation for warping gray matter and white matter images will be determined using the Diffeomorphic Anatomical Registration using Exponentiated Lie algebra (DARTEL) toolbox [53]. Gray matter and white matter images will be smoothed and registered to the standard Montreal Neurological Institute (MNI) space.

#### Brain responses to the WM task and connectivity analyses

T2*-weighted BOLD images will be pre-processed including physiological artifact correction (AFNI, RETROICOR), head motion correction (FSL, mcflirt), and non-brain extraction (FSL, bet). Co-registration between functional and structural images will be performed using boundary-based registration (FreeSurfer, bbregister). The aligned BOLD data will then be registered to MNI space (FSL, fnirt). Spatial smoothing and temporal high-pass filtering will also be performed. General linear modeling (FSL, feat) will yield a brain response map for the WM task in each participant. For functional connectivity analyses, we will use dual-regression independent component analysis and seed-voxel correlation approaches.

#### Diffusion tensor imaging (DTI) analysis

Diffusion-weighted images will be aligned to the b_0_ image to correct for eddy current distortion and then non-brain extraction will be performed. Using FSL’s Diffusion Toolbox (FDT, FSL), a fractional anisotropy map will be computed along with the mean, radial, and axial diffusivity maps, which fit a DTI tensor model. These DTI metric maps will be aligned to the MNI space FMRIB58 FA map.

### Statistical analysis

In this study, statistical analyses will be performed by an independent statistician using full analysis set (FAS) and per-protocol (PP) analyses. The FAS refers to a set that is almost identical to the intention-to-treat (ITT) ideal of including all randomized subjects, but may exclude subjects who never received the treatment or missed baseline measurement after randomization. In addition, we will perform supplementary analysis of the PP analysis group. The PP analysis group refers to a set of subjects who completed the treatment originally allocated. Compliance in this study is deemed to be satisfied only by those who have undergone more than 70% of the total number of acupuncture treatments. In other words, out of the 24 treatments, participants who do not receive treatment more than 17 times are excluded from the PP analysis group because of violation of the protocol.

All demographic and baseline characteristics of participants will be presented based on descriptive analyses. Continuous data will be presented as the average and SD and analyzed using the independent two-sample *t* test or Wilcoxon rank sum test. Dichotomous data will be presented as frequency and percentile and analyzed using the chi-square test or Fisher’s exact test.

Post-test scores will be analyzed using analysis of covariance (ANCOVA), using each group as the fixed factor and baseline score with strata factors (such as sex and age) as the covariate. Within a group, the difference pre-treatment and post-treatment will be compared using the paired *t* test or Wilcoxon singed rank test for continuous data and the chi-square test or Fisher’s exact test for dichotomous data. For repeated measures outcomes, repeated measures analysis of variance (ANOVA) will be performed to compare differences between the times of measurement.

Statistical analyses of clinical outcomes will be performed using SAS® Version 9.4 (SAS Institute, Inc.). All tests will be two-sided and a *p* value <0.05 will be considered statistically significant. We will use multiple imputations for missing data.

Statistical comparisons of data on MRI outcomes will be performed differently. Voxel-wise generalized linear model (GLM) analysis will be performed to compare gray matter volumes within and between groups while controlling for age and sex. Statistical maps of comparisons in gray matter volumes will be corrected for multiple comparisons using the false discovery rate (FDR, *p* < 0.05). Similar to gray matter volumes, differences in brain responses to the WM task and functional connectivity from the resting state fMRI at baseline will be assessed between groups using the independent samples *t* test and voxel-wise GLM analysis (FSL, feat). fMRI metrics between baseline and post-treatment will be compared using the paired samples *t* test in a voxel-wise GLM. Age and sex will be added to the GLM as regressors of no interest. Correction for multiple comparisons of fMRI metrics will be performed using a corrected cluster-size threshold of *p* < 0.05. Statistical comparisons The DTI metric maps will be statistically compared within and between groups using a non-parametric permutation test with 5000 permutations. For multiple comparisons across voxels in DTI metric maps, family-wise error correction will be used with threshold-free cluster enhancement (Randomise, FSL). Whole-brain linear regression analyses will be performed to test association between metrics of cognitive function and changes in brain function and structure. This trial will enroll 50 patients with MCI and this could be a cohort with heterogeneous cognitive function. Thus, we will follow up the aforementioned analyses to evaluate brain function and structure in subgroups with different cognitive functions at baseline. We will divide patients with MCI into equal sample sizes of low-cognitive and high-cognitive function subgroups using the MoCA-K. We will compare between MRI outcomes for low-cognitive and high-cognitive function to test whether cognitive function affects brain function and structure groups, using the independent samples *t* test with identical multiple comparisons correction, as previously described.

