### Outcome measurement

#### Primary outcome

The primary outcome is change in the Digit Span Test (DST) score from baseline to the end of treatment. The DST is used to measure WM, attention, and concentration, and is included in the Wechsler Intelligence Scale [35, 36]. Participants will hear sets of numbers and be asked to recall the numbers forwards or backwards. The digit sequences will be progressively longer until participants cannot recall the sets of numbers twice for a particular sequence length. The DST score is calculated by summation of the maximum number of digits successfully recalled forwards and backwards. The DST will be conducted at baseline, 4 weeks, 8 weeks, and within 2 weeks of the end of treatment.

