### Sample size calculation

To assess the efficacy of the intervention, the minimal clinically important difference (MCID) of DST was considered. However, there was no well-established prior study to derive the MCID of DST. Thus, the effect size was calculated from a similar study examining acupuncture treatment for MCI.

The sample size is estimated based on the result from a previous study [29]. The mean difference in the DST score is assumed to be 0.87 and the standard deviation (SD) of that is assumed to be 0.89 between the acupuncture group and sham acupuncture group. Sample size calculation shows that a total of 44 patients is needed for 90% statistical power and 5% significance level. With an estimated dropout ratio of 10%, the necessary sample size is 50 patients (25 patients for each acupuncture group).

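### The repeated-measures ANOVA for DST and DSST compares visits rather than arms, and paired dichotomous data are given tests for independent samples

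*Protocol article*

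**What the plan says.** All references are to the Protocol article.

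- **Schedule (Primary outcome).** "The DST will be conducted at baseline, 4 weeks, 8 weeks, and within 2 weeks of the end of treatment". Under Secondary outcomes, DSST has the same four assessments. These are the two named outcomes with assessments at 4 and 8 weeks.
- **Between-arm test (Statistical analysis).** "Post-test scores will be analyzed using analysis of covariance (ANCOVA"), with group as fixed factor and the baseline score plus the stratification factors as covariates.
- **Repeated outcomes (Statistical analysis).** "repeated measures analysis of variance (ANOVA) will be performed to compare differences between the times of measurement". The sentence mentions neither group nor a group-by-time interaction.
- **Within-group change (Statistical analysis).** Continuous data get the paired t test or the signed rank test. The same sentence then prescribes "the chi-square test or Fisher’s exact test for dichotomous data".
- **Objective (Objectives).** The first aim is the specific effect of acupuncture relative to sham, which is a between-arm question.

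**The concern.** Each of the two rules fails to fit its question or its data.

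**Repeated outcomes.** A test of differences between visits asks whether scores moved over time. It does not ask whether they moved more under acupuncture than under sham. The trial collects DST and DSST twice during treatment, yet the one analysis named for repeated outcomes does not use those scores to compare the arms. A shared rise is also foreseeable here: a digit test given four times can show practice gains, and the Discussion itself warns of large non-specific effects of sham needling. Such a rise would give a small p-value that says nothing about acupuncture.

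**Paired dichotomous data.** Pre- and post-treatment values come from the same patients. Chi-square and Fisher's exact tests of two proportions assume independent samples, so the standard error is wrong whenever the two values are correlated. The same sentence respects the pairing for continuous data.

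**Working it through.** **1. The plan's own figure.** Sample size calculation uses an SD of 0.89 and states: "The mean difference in the DST score is assumed to be 0.87". With two-sided 5% and 90% power:

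n per arm = 2 × (1.960 + 1.282)² × (0.89 / 0.87)² = 21.99, so 22 per arm and 44 in total.

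This matches "a total of 44 patients is needed for 90% statistical power and 5% significance level". Allowing 10% dropout, 22 / 0.9 = 24.4, so 25 per arm and 50 in total, also as stated. The calculation rests on a single between-arm DST difference, and nothing below changes it.

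**2. What the time test detects when the arms do not differ.**

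Inputs from the protocol: 25 per arm, 4 assessments, two-sided 5%, SD 0.89.

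Assumptions, because the protocol gives no figures:
- 0.89 is the SD of the baseline-to-end change within each arm;
- correlation between visits is equal (compound symmetry);
- the common gain builds up linearly to a total of g at the end of treatment;
- no data are missing.

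Under compound symmetry the within-patient error variance is 0.89² / 2 = 0.396. The visit means lie at 0, g/3, 2g/3 and g. The F test for time has 3 and (50 − 2) × 3 = 144 degrees of freedom, with noncentrality 50 × (sum of squared deviations of the visit means) / 0.396.

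| Common gain g | Sum of squares | Noncentrality | P(time test p < 0.05), analytic | Simulated, 3000 trials per setting, correlation 0.3 to 0.9 |
|---|---|---|---|---|
| 0 | 0 | 0 | 5% | 5.1–5.4% |
| 0.25 | 0.0347 | 4.38 | 38% | 37–39% |
| 0.5 | 0.1389 | 17.5 | 95% | about 95% |

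In the same simulations ANCOVA of the end-of-treatment score, adjusted for baseline, rejected in about 4–6% of trials, close to its nominal level whatever the common gain. The time test responds to the shared drift and the ANCOVA does not.

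**3. Ignoring the pairing.** Take n = 25 patients, proportion 50% at both times and within-patient correlation r (all but n assumed). The unpaired test takes the variance of the difference as 2 × 0.25 / 25. The true variance is that value times (1 − r). The z statistic therefore has SD √(1 − r), and the large-sample rejection rate is P(|Z| > 1.96 / √(1 − r)).

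| r | Large-sample formula | Simulated, 10,000 runs: unpaired chi-square | Simulated: asymptotic McNemar | Simulated: exact McNemar |
|---|---|---|---|---|
| 0.3 | 1.9% | 2.7% | 4.4% | 2.1% |
| 0.5 | 0.6% | 0.9% | 5.1% | 1.3% |
| 0.7 | 0.03% | 0.07% | 4.2% | 0.35% |

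For a true shift from 40% to 70% at r = 0.5, simulated power is 66% for unpaired chi-square, 76% for exact McNemar and 91% for asymptotic McNemar. At r = 0.3 the figures are 64%, 60% and 70%, so the exact version does not always gain power at this size.

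**4. Reach of point 3.** The clinical outcomes under Outcome measurement are scores, and working-memory performance is measured by accuracy rate and response time. No dichotomous pre/post efficacy outcome is defined.

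**The case against.** The strongest reply is that the primary comparison is already sound. The primary outcome is the baseline-to-end change in DST, the ANCOVA adjusts the end score for baseline and strata, and the sample size is built on one between-arm difference. Nothing makes the repeated-measures ANOVA confirmatory, and as a description of the time course it is not wrong in itself. All of this stands, and it limits the point to the supportive analyses.

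It could also be said that post-test scores might include those at weeks 4 and 8, so that ANCOVA would compare the arms there too. The text does not say so, and the sentence written for repeated outcomes names another method and another contrast.

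The 95% figure is, fairly put, the power to detect a gain that was built into the simulation. It shows what the test responds to. It does not predict this trial, and with no common gain the rate is 5%.

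On the dichotomous data, the reply that the consequence is small also stands: with positive correlation the unpaired comparison of proportions is conservative, and no listed efficacy outcome uses it.

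Three stronger readings are tempting, and the protocol does not support them:
- **That DST has two routes to a positive result, so the 5% error is exceeded.** It is true that "All tests will be two-sided and a *p* value <0.05 will be considered statistically significant". But an ANOVA that compares only times is not a test of treatment. The inflation would need a group or group-by-time term that the plan never names.
- **That the ANOVA will drop incomplete cases.** The same section plans multiple imputation.
- **That the dichotomous rule will produce many false positives.** This would need the test to be run for association on the pre-by-post table. The wording, which concerns the pre/post difference, does not point to that layout.

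**Conclusion.** The point holds in a limited form. As worded, the repeated-measures ANOVA gives no acupuncture-versus-sham comparison of the week-4 and week-8 DST and DSST scores, and it can be significant through a change shared by both arms: about 37–39% of trials for a common gain of 0.25 points and about 95% for 0.5. Those rates rest on the assumptions listed under the calculation. The missing between-arm contrast rests on the wording alone.

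Chi-square and Fisher's exact test are the wrong family for paired dichotomous data whatever is assumed about correlation, but the practical effect here is small.

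Neither fault touches the validity of the primary ANCOVA or the 44 and 50 patients. The main gain from a correction is a usable arm-by-visit contrast.

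**What to change.** - Keep the ANCOVA of end-of-treatment DST, adjusted for baseline and strata, and state that it is the primary test.
- For DST and DSST, replace the time-only ANOVA with a supportive repeated-measures model of the post-baseline scores containing baseline, arm, visit, arm-by-visit, sex and age. A mixed model with unstructured covariance would do, as would a repeated-measures ANOVA with group-by-time and a sphericity correction. Report the arm difference at each visit.
- For any within-arm dichotomous pre/post change, use McNemar's test in place of chi-square or Fisher's exact test, and say whether the exact or asymptotic version applies.

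Sample size, visits and data collection stay as they are. The cost is a few sentences of text and slightly more analysis work. These are standard methods and need no special software.

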### Randomization, allocation concealment, and blinding

Subjects will be randomly assigned to either the acupuncture or sham acupuncture group. Stratified block randomization will be used to control the influence of age and sex. An independent statistician who is not related to the intervention practice and outcome assessment will generate a random sequence using SAS® Version 9.4 (SAS Institute, Inc., Cary, NC, USA). This study will be conducted using a central randomized competitive recruitment method. Participants signing the informed consent form voluntarily and meeting the inclusion criteria will be eligible for randomization. An investigator will then assign the participants to groups based on the random sequence prepared and sent by an independent statistician via e-mail.

In this clinical trial, participants and assessors will be blinded to treatment allocation to decrease the risk of bias from the assigned acupuncture treatment group. However, practitioners will not be blinded. The participants will be informed that they will be treated either by real or sham acupuncture before they sign the informed consent form. The validity of the participants’ blinding will be assessed by an investigator who is not involved in either the patients’ allocation procedure or performance of the acupuncture treatment. The assessor will be blinded to the treatment group and prevented from speaking with the participants. Unblinding should be determined on a case-by-case basis and considered only in a critical medical emergency.

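### Head size is not handled in the cross-sectional gray-matter comparisons: it can confound the low/high MoCA-K contrast and costs precision between the randomised arms

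*Protocol article*

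**What the plan says.** The imaging part of the Statistical analysis section of the protocol article fixes the gray-matter model by naming its covariates. A voxel-wise linear model will "compare gray matter volumes within and between groups while controlling for age and sex". On multiplicity it says: "Statistical maps of comparisons in gray matter volumes will be corrected for multiple comparisons using the false discovery rate".

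The same section adds a subgroup step: "We will divide patients with MCI into equal sample sizes of low-cognitive and high-cognitive function subgroups using the MoCA-K". The two halves are then compared on MRI outcomes "to test whether cognitive function affects brain function and structure groups", using the "independent samples *t* test with identical multiple comparisons correction, as previously described". What is expressly carried over is the multiplicity correction. No covariate is named for this step.

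The section on voxel-based morphometry describes the image processing. It states: "Tissue classification, registration, and bias correction will be processed in a generative model". After the DARTEL warping it states: "Gray matter and white matter images will be smoothed and registered to the standard Montreal Neurological Institute (MNI) space". It mentions neither modulation (preserving volume through the warp) nor scaling for head size. Total intracranial volume, head size and brain size appear nowhere in the article, including its abbreviation list.

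**The concern.** Regional gray-matter volume rises with head size. When different people are compared on volume at one time, part of the difference reflects how large their heads are. Age and sex capture only some of this.

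The consequence depends on how the groups were formed:

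- **MoCA-K halves.** These are defined by a patient characteristic, so randomisation gives no protection. If head size is related to the MoCA-K score at all, the halves differ systematically in head size. Regional volume can then differ between them even where cognition has no relation to regional structure. The false discovery rate correction deals with the number of voxels and does not remove this.
- **Randomised arms, cross-sectional volumes.** Head size adds error variance and may be imbalanced by chance. It does not bias the comparison.
- **Within-person change.** Head size is nearly constant in an adult over 12 weeks, so it largely cancels.

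Structural brain change is a listed secondary outcome and serves the second aim, the neurological mechanism. The Discussion also says the MRI results may point to an acupuncture-specific pathway even if the overall effect does not differ between arms. An avoidable nuisance source is therefore worth removing, although the outcomes concerned are secondary and exploratory.

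**Working it through.** **The plan's own figure.** The only sample-size figure is for the Digit Span Test (difference 0.87, SD 0.89, 90% power, two-sided 5%). Per arm: 2 × (1.960 + 1.282)² × (0.89/0.87)² ≈ 22, so 44 in total. Allowing for 10% dropout, 44/0.9 = 48.9, hence 49, rounded up to 50 for equal arms. The figure reproduces and this point does not affect it. No sample size is given for the MRI outcomes.

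**Inputs.**
- From the article: 50 patients, 25 per arm; about 25 per MoCA-K half if all are scanned; two-sided 5%; age and sex as gray-matter covariates.
- Assumed, because the documents give no figure: R², the share of regional volume variance explained by head size after any age and sex adjustment, 0.10 to 0.50; ρ, the correlation of head size with MoCA-K, 0.1 to 0.3.

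**1. Randomised arms, cross-sectional contrast.** Leaving head size out multiplies the standard error by 1/√(1 − R²). For a contrast that has 80% power unadjusted, power with adjustment is Φ[(1.960 + 0.842)/√(1 − R²) − 1.960].

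| R² | SE factor | Power without → with head size |
|---|---|---|
| 0.10 | 1.05 | 80% → 84% |
| 0.25 | 1.15 | 80% → 90% |
| 0.50 | 1.41 | 80% → 98% |

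The chance imbalance in head size has standard error √(1/25 + 1/25) = 0.283 SD. An imbalance of 0.3 SD, about one standard error, shifts the volume contrast by 0.3 × √R², that is 0.09 to 0.21 SD. In a null simulation at one location (N = 50, 10,000 runs) the type I error was 4.7% to 5.0% without head size and 5.1% to 5.5% with it. The unadjusted test already allows for this imbalance.

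**2. MoCA-K halves.** The same null simulation was run with patients split at the MoCA-K median and cognition having no effect on volume. Type I error of the plain t test:

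| ρ | R² = 0.10 | R² = 0.25 | R² = 0.50 |
|---|---|---|---|
| 0.1 | 5.3% | 5.7% | 6.7% |
| 0.2 | 5.9% | 8.4% | 12.4% |
| 0.3 | 7.6% | 13.4% | 20.6% |

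With head size as a covariate it was 4.6% to 5.5% throughout.

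A hand check of the extremes: splitting a normal score at its median separates the halves by 2√(2/π) = 1.596 SD, so head size differs by 1.596ρ and volume by 1.596ρ√R².
- At ρ = 0.3 and R² = 0.50 this is 0.339 SD, or 0.339/0.283 = 1.20 standard errors. The normal approximation gives a rejection rate of about 22%, near the simulated 20.6%.
- At ρ = 0.1 and R² = 0.10 it is 0.050 SD, or 0.18 standard errors, giving about 5.4% against the simulated 5.3%.

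These rates are for a single location. They are not error rates for a whole corrected map.

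**The case against.** **The structural outcome is change.** The Abstract lists structural and functional brain changes, and the Discussion speaks of comparing changes in MRI metrics between arms. Head size largely cancels there. This stands, and it limits the between-arm point to contrasts of volume at one time. The gray-matter sentence does not restrict itself to change, and the next step on functional metrics, introduced as similar, is a between-group comparison at baseline.

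**Randomisation prevents confounding between arms.** The allocation section says: "Stratified block randomization will be used to control the influence of age and sex". The model adjusts for both. This also stands. A reader might infer that acupuncture-versus-sham structural results are confounded by head size. The documents do not support that: the type I error stays near 5%, and only precision is lost.

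**The t test may not be bare.** Elsewhere the section uses t-test names for contrasts fitted inside the linear model with age and sex, and the subgroup step is introduced as following up the earlier analyses. Carry-over of age and sex is a fair reading, so it cannot be asserted that the comparison has no covariates. Head size is absent on either reading.

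**A journal article condenses image processing.** Global scaling could be specified in a fuller imaging plan. The point is therefore conditional on volume-preserving images without scaling. It remains a finding because the article states a specific covariate list.

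**The magnitudes are assumed.** True. At ρ = 0.1 the inflation is slight (5.3% to 6.7%). Eligibility also requires a MoCA-K score below 23, and such a restricted range tends to weaken correlations, which favours the lower part of the table.

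**Conclusion.** The concern holds in a limited form and is minor.

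- **MoCA-K comparison of gray matter:** real risk of confounding, because the halves are not randomised and head size is omitted even if age and sex are carried over. The false-positive rate at one location runs from about 5% to 21% over the assumed ranges (ρ 0.1 to 0.3, R² 0.10 to 0.50), against about 5% with adjustment.
- **Cross-sectional comparison of the randomised arms:** lost precision and exposure to chance imbalance, with a standard error 1.05 to 1.41 times larger for R² of 0.10 to 0.50. It is not biased.
- **Within-person change:** little to gain.

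All of this assumes that the images carry volume information, as the term gray matter volumes implies, and that no head-size scaling is applied. Every magnitude rests on correlations the documents do not supply. The Digit Span primary analysis is unaffected.

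**What to change.** In the imaging part of the Statistical analysis section:

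1. Add total intracranial volume, obtained from the tissue segmentation already planned in SPM, as a nuisance covariate in every cross-sectional gray-matter model. Alternatively, state that volumes will be proportionally scaled to it. Say which, and say whether the images are modulated.
2. Run the low/high MoCA-K comparison of gray matter as a linear model with age, sex and total intracranial volume, in place of the independent samples t test, keeping the planned false discovery rate correction.

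The cost is a sentence or two and no new data. It takes one degree of freedom in any model that already has age and sex. If the MoCA-K t test is read as having no covariates, moving to the full model takes three (48 to 45 with 50 patients).
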